## Abstract

**Background:**

Bell’s palsy is an acute peripheral facial neuropathy, which is one of the most common causes of facial palsy of lower motor neurons. Facial nerve swelling is commonly observed in Bell’s palsy. Acupuncture therapy has been widely used in the treatment of Bell’s palsy. However, whether acupuncture can be effectively used in the acute stage is still controversial. There are no clinical trials conducted previously to evaluate the effect of acupuncture on facial nerve edema in Bell’s palsy patients. The study aims to evaluate the potential efficacy of different acupuncture modalities on Bell’s palsy patients in the acute phase, its effect on facial nerve edema, and to preliminarily explore its possible mechanism.

**Methods and analysis:**

In this randomized, controlled trial, 165 Bell’s palsy patients with unilateral onset within 3 days will be recruited and randomly assigned to either the electroacupuncture group (*n* = 33), the acupuncture group (*n* = 33), the sham acupuncture group (*n* = 33), the blank control group (*n* = 33), or the acupuncture control group (*n* = 33) in a 1:1:1:1:1 ratio. The participants will receive 4 weeks of treatment and 8 weeks of follow-up. The five groups of participants will receive the following treatments: A: Electroacupuncture + Medication (prednisone acetate tablets, mecobalamin tablets, and vitamin B1 tablets); B: Acupuncture + Medication; C: Sham Acupuncture + Medication; D: Medication only; and E: Acupuncture only. The primary outcome will be the effectiveness rate of different acupuncture modalities in improving facial nerve function after the intervention period. The secondary outcomes will be the recovery speed, the diameter of the facial nerve, the echo intensity and thickness of facial muscles, blood flow parameters of the facial artery, the serum inflammatory level, safety evaluation, and adverse events. Preliminary exploration of its mechanism of action occurs through inflammation and immune response. The difference between groups will be assessed using repeated measure analysis of covariance (ANCOVA) and trend chi-square.

**Discussion:**

The trial will evaluate the efficacy and facial nerve edema of acupuncture for Bell’s palsy patients in the acute phase and preliminarily explore its possible mechanism. The results thus may provide evidence for clinical application.

**Clinical trial registration:**

https://www.chictr.org.cn/bin/project/edit?pid=133211, identifier ChiCTR2100050815.

## Introduction

Bell’s palsy is an acute peripheral facial neuropathy, which is one of the most common causes of facial palsy of lower motor neurons (1). Bell’s palsy is defined as an acute unilateral facial nerve palsy or paralysis, with an onset time of less than 72 h, and has unknown etiology. It accounts for 50% of all facial nerve paralysis cases (2), and the incidence rate has been reported between 11.5 and 53.3 per 100 thousand persons (3). The facial nerve is the longest nerve in the human body that traverses through the bone canal, and thus, its anatomical characteristic makes it easy to cause local blood circulation obstacles after an injury and cause nerve edema. The etiology of Bell’s facial palsy remains unclear. The only confirmed finding is that the inflammation and edema of the facial nerve in the narrow styloid foramen can lead to the compression of the facial nerve canal. Facial nerve swelling is commonly observed in Bell’s palsy and has been reported during decompression surgery (4, 5). The different stages of facial palsy are defined as follows: acute phase: 1–7 days; resting phase: 8–20 days; and recovery period: 21–70 days (6). Acupuncture has been widely used in the treatment of Bell’s palsy and has achieved satisfactory results to date (7). Several clinical and laboratory studies have found that acupuncture can effectively promote the recovery of facial nerve injury, effectively shorten the course of the disease, and reduce various complications (8, 9). Especially in Asian countries, such as Korea, Japan, and China, there are a large number of patients who have been managed by acupuncture therapy as the initial treatment. The findings of clinical practice in our department and some prior studies have proved that early use of acupuncture in acute Bell’s palsy can significantly slow down the progress of facial nerve injury, improve the curative effect, shorten the clinical recovery time, and thus reduce the sequelae (10, 11). “Clinical Guidelines for diagnosis and treatment of Traditional Chinese Internal Medicine” and other guidelines made a Grade A recommendation that acupuncture should be involved in the treatment of facial palsy as soon as possible, and the patients with mild or severe facial palsy may be treated with any one of acupuncture, western drugs, or acupuncture combined with drugs (12). However, some experts usually do not accept acupuncture as the recommended strategy for the management of the acute stage of facial nerve injury, possibly because they are afraid that the potential application of acupuncture in the acute stage can aggravate nerve edema (2). However, Fang et al. have used thick needle therapy to treat acute ischemic facial nerve injury in rats. It was found that the swelling degree of the facial nerve in the treatment group was markedly lower than the control group on days 1, 3, 5, and 7, which promoted the regression of the facial nerve edema in the bone canal (13). However, there is no prior report on the potential effects of acupuncture for facial edema in patients with acute Bell’s palsy.

For the objective quantification of the facial nerve edema, enhanced magnetic resonance imaging (MRI) can be effectively used to observe facial nerve ischemia and edema, but it is actually contrast-enhanced rather than physical nerve swelling, which is costly, time-consuming, and associated with many limitations (14, 15). Neuroultrasound is a non-invasive examination method to objectively describe facial nerve edema. It can facilitate real-time image acquisition to describe the structural changes of the nerve and has the advantages of cheap price, easy access, and bedside use (16). In addition, pathological studies have confirmed that local ischemia of the affected lateral nerve in patients with Bell’s palsy could be often observed. Because the direction of blood flow of the facial nerve is mainly from proximal to distal, the microcirculation of facial skin might also get adversely affected after Bell’s palsy attack (17). For example, Yin et al. (18) observed the potential changes in the blood flow at the facial acupoints of patients with Bell’s palsy by Doppler ultrasound and found that there were significant differences in the average velocity, final diastolic velocity along the maximum velocity curve, peripheral resistance index at the four facial acupoints between the affected side and the healthy side, and between patients with different facial palsy degrees. Therefore, color Doppler ultrasound can dynamically and quantitatively monitor the changes in the facial artery blood flow parameters in patients with Bell’s facial palsy during acupuncture treatment, which can be used as an important basis for the analysis of observed curative effects.

At the same time, ultrasound can also evaluate the muscle condition of patients with facial palsy by observing the area, depth, and echo intensity of facial muscles. Volk et al. used quantitative muscle ultrasound to assess the muscle area, thickness, and echo intensity of 2 masticatory muscles and 6 facial muscles in 20 patients with chronic facial palsy. The results showed that the lateral muscles of the paralyzed side decreased significantly, and the echo intensity of other facial muscles increased markedly except that of the frontalis and orbicularis oculi muscles (19).

Therefore, we have designed a randomized controlled trial (RCT) to examine the possible efficacy of different acupuncture modalities on patients with Bell’s palsy in the acute phase and the improvement of facial nerve edema using appropriate randomization and rigorous blinding conditions. The objectives of this trial are as follows:

To evaluate the efficacy of different acupuncture modalities on patients with Bell’s palsy in the acute stage;To assess whether different acupuncture modalities can effectively relieve facial nerve edema in patients with Bell’s palsy in the acute stage;To analyze whether different acupuncture modalities can significantly improve facial blood circulation and muscle activity in patients with Bell’s palsy in the acute stage;To provide reference for the timing of different acupuncture modalities intervention;To explore the mechanisms that can contribute to both inflammatory and immune responses.

## Methods and analysis

### Study design

This will be a single-center, randomized, controlled clinical trial. The study has been approved by the ethics committee of the First Affiliated Hospital of China Medical University (CMU1H). It will be conducted from October 2021 to December 2025 in the Traditional Chinese Medicine (TCM) Department, Emergency Department, Ultrasound Department, and Neurology Department of CMU1H, which is the largest comprehensive hospital in northeast China. All the participants will be informed about the study and sign written informed consent before participating in the trial. Eligible patients will then be randomly divided into the electroacupuncture group (EA + medicine), the acupuncture group (A + medicine), the sham acupuncture group (SA + medicine), the blank control group (pure medicine), and the acupuncture control group (pure acupuncture) at a ratio of 1:1:1:1:1. The first three groups will be treated with electroacupuncture, acupuncture, or sham acupuncture five times a week based on medicine therapy. The blank control group will be treated with medicine only, and the acupuncture control group will be treated with acupuncture five times a week without medicine-based treatment. The treatment course will last for 4 weeks and thereafter follow up for 8 weeks. This trial is designed in strict accordance with the Consolidated Standards of Reporting Trials (CONSORT) statement and the recommendations of Standards for Reporting Intervention in Controlled Trials of Acupuncture (STRICTA) (20) and will be reported based on the Standard Protocol Items: Recommendations for Interventional Trials (SPIRIT) 2013 Checklist (21). The trial flow chart is shown in Figure 1, and the study design schedule is shown in Table 1. Supplementary material S1 contains the complete spirit list.

**Figure 1 fig1:**
[figure not shown]
Flow chart of the planned study. EA: electroacupuncture; A: acupuncture; SA: sham acupuncture; BC: blank control; and AC: acupuncture control.

**Table 1 tab1:** The designed schedule for the data collection.

Time point	Screening period	Intervention period					Follow-up period	
	Day 0	Day1	Day 5 (Week1)	Day 10 (Week2)	Day 20 (Week4)	Once daily until discharge	Week 8 ± 3 days	Week 12 ± 3 days
Enrolment								
Informed consent	×							
Eligibility screening	×							
Randomization	×							
Allocation	×							
Interventions								
The electroacupuncture group								
The acupuncture group								
The sham acupuncture group								
The blank control group								
The acupuncture control group								
Assessments								
SFGS	×		×	×	×	×	×	×
HBGS	×		×	×	×	×	×	×
The diameter of facial nerve	×		×	×	×		×	×
Echo intensity and thickness of facial muscles	×		×	×	×		×	×
Blood flow parameters of the facial artery	×		×	×	×		×	×
Therapeutic mechanism index	×		×	×	×		×	×
Safety index	×		×	×	×			
Adverse events			×	×	×	×		
Success of blinding					×			

The treatment course will last for 20 days (4 weeks) and thereafter follow up for 8 weeks. First, the subjects will be informed of informed consent and screening. Then, they will be randomized into five different groups. The four groups related to acupuncture will be treated with acupuncture 5 times a week for a total of 4 weeks (20 days); the blank control group will receive the medicine therapy (see “Intervention” for details). The clinical data will be evaluated at baseline, days 5, 10, and 20 (weeks 1, 2, and 4), and weeks 8 and 12 of treatment. The Sunnybrook facial grading system (SFGS), the House-Brackmann facial nerve grading system (HBGS), and adverse events will be evaluated daily during treatment. During treatment, adverse events will be recorded in the Case Report Form (CRF) at any time.

### Participants

#### Recruitment strategy

The participants of the study will be recruited from the outpatient, emergency, and ward departments of the CMU1H using WeChat advertising and posters. Interested patients can enquire from the clinician about the various details of the project through telephone or direct meetings. The investigator will also describe the purpose, content, research process, benefits, and risks of the study to the participants in detail. The researchers will screen the patients according to the study protocol, and eligible patients will then be recruited for the clinical trials.

#### Inclusion criteria

The study includes the following inclusion criteria:

Participants who aged between 18 and 70 years;Participants who meet the diagnostic criteria for Bell’s palsy, HBGS should be graded from II to VI, and the total score of SFGS should be ≤89;The onset is less than or equal to 3 days;The onset is unilateral; andParticipants who agreed to participate in the investigation and sign the written informed consent.

#### Exclusion criteria

Participants who will meet any of the following conditions will be excluded:

Participants who have otitis media, mastoiditis, labyrinthitis, mumps, and other complications of peripheral facial palsy;Participants who have a prior diagnosis of peripheral facial palsy caused by posterior fossa lesions such as acoustic neuroma, skull base meningitis, intracranial metastasis of cancer, and multiple sclerosis;Participants diagnosed with the central facial palsy;Participants diagnosed with Hunt’s syndrome;Participants with serious cardiovascular and cerebrovascular diseases, diabetes, hypertension, serious primary diseases of the liver, kidney, lung, and blood system, malignant tumors, ulcers of the digestive system, and bleeding tendencies are expected to fail to complete the test;Participants who might be enrolled in other clinical trials within 1 month; glaucoma patients; and pregnant or lactation women or patients with severe allergic conditions. Those who have neurological, mental illness, illiteracy, or poor compliance in the screening process will not be eligible to fill in the questionnaire.

### Sample size

The calculation of the sample size is based on the effective rate of acupuncture in the treatment of patients with Bell’s palsy in the acute stage. According to the previous studies (22, 23) and pre-experimental analysis of the research group, it is estimated that the effective rate of the EA group is 98%, the A group is 95%, the AC group is 85%, the SA group is 74%, and the BC group is 70%. We used PASS 15 software to calculate and set α = 0.05 and β = 0.1, and the results showed that the total sample size was at least 147 cases. It was observed that based on the ratio of the sample size of 1:1:1:1:1 in each group and considering the loss of follow-up rate of 10%, an optimal sample size of 33 participants should be recruited in each group. Therefore, a total of 165 participants should be recruited for this RCT.

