### Statistical analysis

The statistical analysis of this trial will use SPSS 26.0 software. To include the data of the participants who might withdraw later from the trial, all statistical analyses were based on the intention-to-treat population of all randomly assigned patients. Missing data will be analyzed using multiple imputations using the Markov chain Monte Carlo. The continuity data will be described as mean ± standard deviation (SD) or median and interquartile spacing. The classified data will be described with the frequency and percentage (*N*, %). The assessment of the difference between groups will use repeated measure analysis of covariance (ANCOVA) and trend chi-square, and the mixed effect model will also be used to evaluate the efficacy based on adjusting possible covariates. For results that require a comparison between multiple groups, Bonferroni will be used for multiple corrections. An interim analysis will be performed when half of the participants have completed the main outcome measurement.

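### The stated 90% power fits a five-arm any-difference test and does not carry over to the Bonferroni-adjusted comparisons that answer the trial's questions

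*Protocol article*

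**What the plan says.** The Sample size section of the protocol article gives one expected effective rate per arm: electroacupuncture plus medicine (EA) 98%, acupuncture plus medicine (A) 95%, acupuncture alone (AC) 85%, sham plus medicine (SA) 74%, medicine alone (BC) 70%. It then "set α = 0.05 and β = 0.1" and concludes: "the results showed that the total sample size was at least 147 cases". With equal allocation and 10% loss this becomes 33 per arm, 165 in all. No test, contrast or multiplicity allowance is mentioned.

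The Statistical analysis section lists repeated-measures ANCOVA, a trend chi-square and a mixed model, and adds: "For results that require a comparison between multiple groups, Bonferroni will be used for multiple corrections". It does not say how many comparisons that covers.

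The objectives at the end of the Introduction concern the efficacy of different acupuncture modalities. The Discussion gives the sham arm the task of separating a real needling effect from placebo.

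**The concern.** The alpha used to size the trial is the full 0.05, while the alpha for comparing arms will be 0.05 divided by a number not stated. A reader who sees beta 0.1 will attach it to the comparisons of interest. If A against SA or EA against A then comes out non-significant, it is likely to be read as no difference, although the trial had a modest or negligible chance of detecting the difference it assumed. Rejecting equality of all five rates does not fill the gap, because it does not say which arms differ.

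**Working it through.** **Inputs.** Rates 0.98, 0.95, 0.85, 0.74, 0.70; alpha 0.05; power 0.90; 147 evaluable, 165 recruited (Sample size). Bonferroni (Statistical analysis). Assumptions: two-sided tests; 2, 4 or 10 comparisons (10 is all pairs of five arms); 30 per arm after loss (165 × 0.9 / 5 = 29.7), with 33 also shown.

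**Step 1: reproduce 147.** The mean rate p̄ is 0.844. A 4-df chi-square at alpha 0.05 needs non-centrality 15.405 for 90% power.

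- Likelihood-ratio effect per patient: the average over arms of 2[p ln(p/p̄) + (1−p) ln((1−p)/(1−p̄))] = (0.2107 + 0.1110 + 0.0003 + 0.0710 + 0.1305)/5 = 0.1047. Then 15.405/0.10468 = 147.2, so N = 148. Power at 147 is 89.96%.
- Pearson effect size: w² = 0.012264/(0.844 × 0.156) = 0.0931. Then 15.405/0.09315 = 165.4, so N = 166.
- Simulated Pearson test: 90.6% power at 30 per arm.

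Loss: 147/0.9 = 163.3, so 164; 164/5 = 32.8, so 33 per arm and 165 in total, as stated.

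**Step 2: power for pairs of arms.** The statistic is z = |x₁ − x₂|/n ÷ √(2p̂(1−p̂)/n), where x₁ and x₂ are the responders in the two arms and p̂ is the pooled rate. The pair is significant if z exceeds the two-sided critical value at 0.05/m (2.241, 2.498 and 2.807 for m = 2, 4, 10). Exact power sums the binomial probabilities of all significant outcomes.

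| Pair | n | Unadjusted | m = 2 | m = 4 | m = 10 |
|---|---|---|---|---|---|
| EA–BC | 30 | 92.8% | 87.1% | 78.8% | 62.4% |
| EA–SA | 30 | 86.5% | 77.5% | 65.6% | 47.2% |
| A–BC | 30 | 77.8% | 68.3% | 57.3% | 40.2% |
| A–SA | 30 | 66.5% | 55.1% | 43.1% | 26.7% |
| EA–A | 30 | 3.5% | 0.9% | 0.2% | <0.1% |
| EA–BC | 33 | 95.0% | 90.8% | 84.4% | 64.4% |
| A–SA | 33 | 70.9% | 60.3% | 49.0% | 27.6% |

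Hand check by normal approximation, A–SA, m = 4, n = 30: null SE √(2 × 0.845 × 0.155/30) = 0.0934; alternative SE √((0.95 × 0.05 + 0.74 × 0.26)/30) = 0.0894; Φ((0.21 − 2.498 × 0.0934)/0.0894) = Φ(−0.26) = 40%, close to the exact 43%.

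**Step 3: what 90% would need.** By normal approximation, EA–SA needs 58 evaluable per arm with four comparisons and 68 with ten; A–SA needs 83 and 97.

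**Step 4: an example of a shorter list.** Holm over EA–SA, A–SA, EA–BC and A–BC, simulated at 30 per arm: about 74%, 57%, 83% and 68% with the uncorrected chi-square. With Fisher's exact test: about 57%, 39%, 70% and 51%.

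**The case against.** Three stronger readings are tempting, and the document supports none of them.

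- *The sample size is miscalculated.* It is not. The 147 agrees with a five-arm test, the loss allowance is correct, and the Pearson formula's 166 is a different approximation to the same test.
- *Pairwise power is 0 to 62%.* That assumes all ten pairs and 30 per arm, and the protocol fixes neither. Shorter families do better. The intention-to-treat analysis with multiple imputation would include all 33 per arm, where EA–BC with two comparisons reaches 91%. Unadjusted, EA–BC has 93% at 30 per arm.
- *The 90% can only belong to an any-difference test.* This is an inference, because no test is named. A trend chi-square is in the plan; applied to the arms in their assumed order, it would have about 96% power at 147 by normal approximation.

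It is also fair to say that a condensed article may leave the list of contrasts and the testing procedure to a fuller document. The absence of that list is therefore not the complaint.

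What remains is the mismatch on the page between unadjusted sizing and adjusted comparisons. A trend test does not remove it, since it isolates neither real from sham needling nor EA from A. A–SA falls short even with no adjustment (66.5% at 30 per arm, 70.9% at 33).

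**Conclusion.** The point holds as one of sample size and multiplicity, and it should be fixed. The stated power is consistent with a global five-group test and is not delivered for the adjusted comparisons the trial exists to make. At 30 per arm no adjusted pair reaches 90% with two or more comparisons. At 33 per arm only EA–BC does, and only in a family of two. A against sham lies between 27% and 60% over the family sizes and arm sizes shown. EA against A has practically no power, because the assumed rates differ by three points.

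These figures rest on the protocol's own rates, two-sided uncorrected chi-square tests and assumed family sizes. Fisher's exact test would lower them.

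**What to change.** In the Sample size section, name the global five-group test as the one to which the 90% applies, and state the adjusted power for each comparison the trial will interpret.

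Before the interim analysis, and in any case before those choosing have seen unblinded results, name a short list of confirmatory contrasts that includes real versus sham. Test them by Holm in place of Bonferroni; Holm keeps the same family-wise error and is never less powerful. Which contrasts to name is the sponsor's choice. The four in Step 4 are only an example: they leave out EA against A, which the modality objective may call for.

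Report the remaining pairs as estimates with confidence intervals, and say that non-significance will not be read as no difference.

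The cost is wording in two sections and no extra patients. The price is a less favourable power statement and some pairs becoming descriptive. Rewording does not restore 90%; for the sham contrasts that would take the larger arms shown in Step 3.

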### Randomization

A random sequence will be generated based on block randomization by an independent research assistant using the software SPSS 26.0. The various eligible participants will be randomly divided into five groups with a 1:1:1:1:1 ratio. The treatment allocation codes will be enclosed by an independent researcher in sequentially numbered opaque envelopes until the first treatment schedule. To minimize coding interruptions, the chief investigator and result evaluators will also turn a blind eye to the treatment allocation.

